### Safety aspects

#### Adverse events

An adverse event (AE) could include an abnormal laboratory finding, symptom, or disease temporally associated with the administration of an investigational product, regardless of whether it is related to that investigational product. In the present study, an unexpected AE is anything that is not identified in nature, severity, or frequency in the Investigator’s Brochure. During routine assessments, the investigator will question the participants about the occurrence of AEs and record the information in the source documents and patient CRF.

#### Serious adverse events

A serious adverse event (SAE) is one which cause death, a life-threatening adverse experience, inpatient hospitalization or prolongation of existing hospitalization, a persistent or significant disability/incapacity, or a congenital anomaly/birth defect. Other important medical events may also be considered SAEs when, based on appropriate medical judgment, they jeopardize the participant or require intervention to prevent one of the outcomes listed.

When AEs occur throughout the clinical trial, investigators may take necessary measures according to the condition of the participant. Based on the severity of the AE, the investigators may choose hospitalization, outpatient treatment, home visits, communication, or other follow-up methods.

### Data and Safety Monitoring Board

The DSMB will review the safety, ethics, and outcomes of the study. It is independent from the sponsor and has no competing interests. DSMB members will monitor blinded assessment data for SAEs or potential harmful effects. A charter that will outline member responsibilities, procedures, and confidentiality will govern the DSMB. The DSMB will also review unblinded data at regular intervals during the follow-up period and will monitor neurological and functional differences between the two groups, as well as drop-out and event rates. Furthermore, the DSMB members will also manage the oversight of the trial progress, such as the status of recruitment and involvement of the sites.

### Data quality and management

Data collection will be restricted to the those who meet the eligibility criteria. Participants who withdraw from the study for any reason will have their data recorded in their medical records and be reviewed by the trial monitor.

#### Data collection and monitoring

CRFs must be completed according to the schedule. All SAEs that occur during the observation period must be reported to the medical expert overseeing the investigation (the medical director of Beijing PINS Medical Co., Ltd). The investigators are responsible for all information collected about participants enrolled in this study. The investigators and sponsor will conduct regular telephone or home follow-up of patients.

The monitoring system will assure the quality of the assessments. The data will be entered into a validated database. The Data Management Group will be responsible for data processing, in accordance with procedural documentation. The database will be locked once quality assurance procedures have been completed.

#### Withdrawal and termination from the study

In case of endangerment of personal safety, lack of compliance, or withdrawal of informed consent, a participant will instantly be excluded from the study. Furthermore, participants will be withdrawn from the study under the following conditions: 1) the participant’s parents require withdrawal; and 2) the participant develops heart failure, respiratory failure, or other serious disease. The DSMB might terminate the study under the following conditions: 1) SAEs occurred during the trial; 2), the investigator determined that the trial should be terminated; and 3) the Ethics Committee require termination.

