### Trial outcomes

#### Primary clinical outcomes

The primary outcome will be stand–walk–sit (SWS) task scores at 3 months compared with the baseline scores. The domain of the SWS score is the gait. The study will compare the mean scores in each group between 3 months and baseline, using the mean scores from each group. The SWS test is a simple and quick functional mobility test that requires an individual to stand up, walk 5 m, turn, walk back, and sit down. The time taken to complete the test is strongly correlated with the level of functional mobility. This test will be videotaped and scored by two blinded neurologists.

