#### Handling of missing data

All variables included in the CRF are mandatory. The method of last-visit-carried-forward will be used to handle the missing data.

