#### Data analysis

All evaluations of effectiveness and safety will be conducted according to the intention-to-treat principle. The final data will be analyzed using IBM SPSS 13.0 or higher (SPSS, Inc., Chicago, IL, USA) and SAS 9.4 or higher (SAS Institute Inc., Cary, NC, USA). A *p* value <0.05 will be considered statistically significant. Data will be analyzed with *t* tests and χ^2^ tests for continuous variables and categorical variables, respectively.

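### Mandatory removal from the study after randomisation sits badly with the promised intention-to-treat analysis, because no passage separates leaving the assigned stimulation from leaving follow-up

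*Protocol article*

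**What the plan says.** All places are in the protocol article.

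- **Withdrawal and termination from the study**, first rule: "In case of endangerment of personal safety, lack of compliance, or withdrawal of informed consent, a participant will instantly be excluded from the study".
- **Same section**, second rule: "participants will be withdrawn from the study under the following conditions", one of which is that "the participant develops heart failure, respiratory failure, or other serious disease".
- **Data quality and management**: "Participants who withdraw from the study for any reason will have their data recorded in their medical records and be reviewed by the trial monitor". This sentence names neither the case report form (CRF) nor the trial database.
- **Data analysis**: "All evaluations of effectiveness and safety will be conducted according to the intention-to-treat principle".
- **Handling of missing data**: "The method of last-visit-carried-forward will be used to handle the missing data".
- **Primary clinical outcomes**: "The primary outcome will be stand–walk–sit (SWS) task scores at 3 months compared with the baseline scores".
- **Table 1** schedules the SWS test at V1 (screening), V2 (upgrade and random grouping), V3 (90 ± 14 days), V4 and V5. V3 is the first visit after the blinded treatment period.

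**The concern.** Intention-to-treat keeps non-compliers and people with intercurrent events in the group to which they were randomised. It needs their outcomes as well as their names on the list. The withdrawal section takes these same people out of the study, and the rule is mandatory. What they leave is the study itself, and no passage distinguishes that from leaving a stimulation setting.

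Lack of compliance, a safety problem or a serious illness may be related to the assigned mode or to how the participant is doing. If so, removal after randomisation is selective. Two things are then at stake. The primary comparison would rest partly on values measured before the 3 months of treatment. The safety comparison would have less observation time in those who had just had a problem. No later analysis can recover an outcome that was not collected.

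**Working it through.** **1. The passages side by side.**

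| Question | What the protocol article gives |
|---|---|
| Who must leave the study? | Non-compliers, those whose safety is endangered, those who withdraw consent, those who develop serious disease |
| Does follow-up continue for them? | Not stated either way |
| Where do their data go? | Medical records, with monitor review; CRF and database not mentioned |
| Who is analysed? | Intention-to-treat, for effectiveness and safety |
| What stands in for a missing V3 value? | The last visit carried forward |

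For anyone removed before V3, Table 1 leaves only V1 or V2 to carry forward. The imputed change from baseline is therefore roughly zero, whatever happened under treatment.

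**2. Number affected.** The Sample size section assumes 10% attrition: 0.10 × 106 = 10.6 participants.

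**3. A range for the SD, which the protocol does not give.** With 53 per arm and 10% loss, 53 × 0.9 = 47.7 are evaluable. The detectable standardised difference is d = (1.960 + z) × √(2/47.7). The section states both 80% and 90% power, so both are used:
- 80%: (1.960 + 0.842) × 0.2048 = 0.574
- 90%: (1.960 + 1.282) × 0.2048 = 0.664

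For a 10-point difference the implied SD is 10/0.664 = 15.1 to 10/0.574 = 17.4. For a 20-point difference it is 20/0.664 = 30.1 to 20/0.574 = 34.9. I therefore take SD 15 to 35 as an assumed range.

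**4. Bias if the worst responders are removed.** Assumptions: no true effect, mean change m = 10 points in both arms (one reading of the placebo allowance), normal changes with SD s, and zero change imputed for those removed. If the worst fraction f is removed, the arm mean becomes (1 − f)m + sφ(z_f), where φ is the normal density at the f-quantile. The VFS minus CFS bias is then

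−m(f_V − f_C) + s[φ(z_fV) − φ(z_fC)].

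With f_V = 0.15 and f_C = 0.05, which average to the planned 10%, φ = 0.2332 and 0.1031, a difference of 0.1300:
- SD 15: −1.0 + 15 × 0.1300 = +0.95
- SD 30: −1.0 + 30 × 0.1300 = +2.90
- SD 35: −1.0 + 35 × 0.1300 = +3.55

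Rounding to whole people (8 and 3 of 53) lowers these a little, to about +2.7 at SD 30.

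**5. False-positive rate, by simulation** (53 per arm, *t* test, error counted in favour of VFS, nominal 2.5%). When everyone below the 15% or 5% quantile is removed, the rate is about 6% at SD 15, 8% at SD 30 and 9% at SD 35. If exactly the 8 and 3 worst are removed, the rate at SD 30 is nearer 10%. The answer depends even on this detail.

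**6. Other removal patterns, same formula.**
- Equal removal, f_V = f_C = 0.10: both terms cancel and the bias is 0.
- Removal unrelated to outcome, 15% v 5%: the second term vanishes, leaving −10 × 0.10 = −1.0. With 8 v 3 of 53 it is −10 × 5/53 = −0.94. The bias is now against VFS.

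**7. Equal removal still has a cost.** If 10% per arm are carried at zero change and the SD is unchanged, the effect shrinks to 0.9d with 53 per arm. Power = Φ(0.9d√(53/2) − 1.960). For d = 0.664 this is about 87% instead of 90%. For d = 0.574 it is about 76% instead of 80%.

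**The case against.** **A literal contradiction is not shown.** One section governs participation and another governs analysis. A reader might infer that removed participants leave the analysis set, but no passage says so, and carry-forward gives a means of keeping them in it. This stands. It leaves the loss of their actual outcome untouched.

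**Instant exclusion for serious illness.** A reader might run the two withdrawal rules together. The word for immediacy belongs only to the first sentence (safety, compliance, consent). Serious disease has its own sentence, without that word, although withdrawal there is still mandatory.

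**Data lost to medical records.** The text does not say that data go only there, and it adds monitor review. The same section limits data collection to eligible people, which reads most naturally as a statement about enrolment. Whether withdrawn participants' data stay in the database is unresolved.

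**Outcomes and harms never collected.** That is inference. The sections on serious adverse events and on data collection provide for follow-up after an adverse event, SAE reporting during the observation period, and telephone or home contact. None of these says it continues after removal, and none says it stops. A videotaped SWS test cannot be done by telephone.

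**Removal need not depend on arm.** Heart or respiratory failure need not relate to stimulation mode, and staff other than the programmer are blinded. This is fair, and it is why the bias is stated only as conditional.

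**Condensed article.** Analysis-set definitions may properly be left to the full protocol or the SAP. The point here is a stated mandatory rule and its consequence, so this does not answer it.

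**Conclusion.** The concern holds in limited form. The protocol makes removal from the study mandatory for non-compliance, endangered safety and serious disease, and it does not separate leaving the assigned stimulation from leaving follow-up. Followed as written, this works against the intention-to-treat promise for the primary endpoint and leaves the recording of harms after removal uncertain. Ending participation because consent is withdrawn is proper and is no part of the problem.

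No single figure for the bias can be defended. About +1.0 to +3.5 points, with one-sided error of about 6% to 9%, is a worst case. It rests on an assumed SD of 15 to 35, a 10-point mean change, unequal removal (15% v 5%) and removal of exactly the worst responders. Change the removal pattern and the bias vanishes or reverses. The figures show what the rule permits and do not predict the trial's result. The bias also works through carry-forward, so it should not be added to any separate criticism of that method.

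**What to change.** Reconcile the sections on withdrawal, data quality and management, and data analysis by stating that:

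1. non-compliance, a safety event or serious illness does not by itself end outcome or AE/SAE collection;
2. all randomised participants are invited to V3 (SWS, questionnaires, AE/SAE) and are analysed in their randomised group;
3. data collected up to withdrawal stay in the CRF and the trial database;
4. only withdrawal of consent to data collection ends collection.

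When a participant's stimulation is changed or stopped is a clinical decision and is not addressed here.

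The cost is a short amendment and some site effort to obtain V3 from participants who would otherwise be dropped. The article's Discussion reports 50 of the planned 106 enrolled, so at that point the change would still have covered at least 106 − 50 = 56 participants from their entry.

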#### Handling of missing data

All variables included in the CRF are mandatory. The method of last-visit-carried-forward will be used to handle the missing data.

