## Design and methods

### Trial design

The RESTEP study (ClinicalTrials.gov, NCT03053726) is a double-blind, randomized, multicenter trial designed to evaluate the safety and effectiveness of STN-VFS treatment in participants with advanced PD. According to the trial flow chart (Fig. 1), participants with advanced PD who had previously undergone DBS will be screened based on strict inclusion and exclusion criteria. A total of five follow-up surveys will be scheduled as shown in Table 1. After recruitment, pulse generators previously implanted in all participants will be upgraded from those with a single mode (CFS only) to those that are capable of dual-mode stimulation (CFS or VFS). Following this upgrade, participants will be randomly and equally divided into two groups: the CFS group and the VFS group. After 3 months of stimulation under the blinded conditions, all participants will receive VFS and follow-up assessments for 6 months. The protocol design is based on the guidelines of the Consolidated Standards of Reporting Trials and Standard Protocol Items: Recommendations for Interventional Trials (SPIRIT) (see Additional file 1), and the study results will also be reported according to these guidelines. Informed consent will be obtained from all participants in accordance with the policies of the board.

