### Randomization and blinding

Eligible participants will be randomly assigned to one of two groups (CFS group or VFS group) after completing the baseline measurements. A 1:1 assignment sequence (based on computer-generated random numbers) will be produced by The Peking University Clinical Research Institute. The computer-generated random numbers will be used to create the participant numbers and order lists, which will be placed in opaque sealed envelopes and sent to the research centers. The research clerk will keep copies of the order lists and participant numbers.

Throughout the study, with the exception of the study programmer, all participants and study staff (including investigators, trainers, and statisticians) will be blinded to the treatment allocation. Independent raters who have no therapeutic relationships with the participants and who are blind to the treatment conditions will conduct outcome assessments. The independent raters will be clinical neurologists who have received additional training on the use of the outcome assessments, had the opportunity to listen to conducted assessments, and received direct feedback regarding their assessments from supervisors. Furthermore, the Data and Safety Monitoring Board (DSMB) will review a random selection of 20% of the recorded assessments. Loss of blinding may occur due to the magnitude of the therapeutic effect or any other subjective perception that indicates that VFS or CFS is delivered.

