### Statistical considerations

#### Sample size

The sample size was calculated based on the primary outcome measure according to the results of our pilot study. Power was set at 80% and calculated based on two-sided 95% confidence intervals. In our pilot data, we detected a post-treatment difference in PD symptoms of at least 20% between the VFS and CFS groups for SWS scores. We assume that the placebo effect can account for about 10% of such differences. We assume that 10% of the trial participants will be lost to attrition. Thus, 53 participants need to be allocated to each treatment group to establish a difference among the treatments at a level of 5% with a power value of 90%.

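### Last-visit-carried-forward, the only missing-data method named, gives anyone lost before the 3-month visit a baseline-phase SWS value and so distorts the primary VFS–CFS comparison

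*Protocol article*

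**What the plan says.** All statements are from the protocol article.

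- Handling of missing data: "The method of last-visit-carried-forward will be used to handle the missing data". No variable or visit is excepted, and no other method is named.
- Primary clinical outcomes: "The primary outcome will be stand–walk–sit (SWS) task scores at 3 months compared with the baseline scores".
- Data analysis: "All evaluations of effectiveness and safety will be conducted according to the intention-to-treat principle", and "Data will be analyzed with *t* tests" for continuous variables.
- Sample size: "We assume that 10% of the trial participants will be lost to attrition". The figure is not split by arm.
- Trial design: "After 3 months of stimulation under the blinded conditions, all participants will receive VFS and follow-up assessments for 6 months".
- Table 1: SWS and UPDRS-III are scheduled at V1 to V5. V1 (screening) and V2 (upgrading) stand under Baseline, and V3 follows at 90 ± 14 days. FOG-Q, GAFQ and PDQ-39 are scheduled at V1, V3 and V5 but not at V4. At V4 and V5 both arms are labelled as on VFS.
- Withdrawal and termination: "In case of endangerment of personal safety, lack of compliance, or withdrawal of informed consent, a participant will instantly be excluded from the study".

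**The concern.** Carry-forward depends entirely on what the last available value represents. Here no SWS test falls between the start of blinded stimulation and the endpoint it is meant to replace. The carried value is from V1 or V2, so it says almost nothing about three months of either treatment. Under intention-to-treat the participant stays in the t test with that value, which is treated as if it had been observed. The estimated difference then depends partly on how many participants each arm loses, and the imputation uncertainty is ignored.

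A second problem arises after V3, when the control arm changes to VFS. For a measure not taken at V4, a control participant who misses V5 has a V3 value, obtained under CFS, entered at a time point when everyone is on VFS.

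At stake are the size of the primary treatment difference, some power, and the meaning of some 6-month secondary results.

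**Working it through.** **What is imputed.** Randomisation takes place "CFS group or VFS group) after completing the baseline measurements", and Table 1 puts SWS at both V1 and V2. The article does not say which of the two is the baseline. If it is V2, the imputed change is exactly zero. If it is V1, the imputed change is the V1-to-V2 change over a few days around the upgrade. The calculations below use zero.

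**The plan's own figure.** The 53 per arm cannot be reproduced because no SD is given. Back-solving with 53 × 0.9 ≈ 48 evaluable per arm at 90% power and two-sided 5%: d = (1.960 + 1.282) × √(2/48) = 0.66. A 20-point difference then implies an SD of about 30. The article also states 80% power, which would imply an SD of about 35. SD 30 is therefore an assumption compatible with the plan, not a documented value.

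**Formula.** Let m be the mean improvement in percentage points and d the proportion lost, with subscripts V (VFS) and C (CFS). With zero imputed, the expected estimate is (1 − dV)·mV − (1 − dC)·mC. If those lost would have done as well as their arm, the truth is mV − mC and the bias is dC·mC − dV·mV.

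**Loss unrelated to outcome** (arm means and split by arm are assumed):

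| mV / mC | Loss VFS / CFS | Truth | Carry-forward |
|---|---|---|---|
| 30 / 10 | 10% / 10% | 20 | 27 − 9 = 18.0 |
| 20 / 10 | 10% / 10% | 10 | 18 − 9 = 9.0 |
| 20 / 10 | 5% / 15% | 10 | 19 − 8.5 = 10.5 |
| 20 / 10 | 15% / 5% | 10 | 17 − 9.5 = 7.5 |
| 10 / 10 | 15% / 5% | 0 | 8.5 − 9.5 = −1.0 |
| 10 / 10 | 5% / 15% | 0 | 9.5 − 8.5 = +1.0 |

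Complete cases are unbiased in every row of this table.

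**Power, first row, SD 30.** The variance after imputation is 0.9 × 900 + 0.09 × m². That is 891 for VFS (m = 30) and 819 for CFS (m = 10). SE = √((891 + 819)/53) = 5.68, and 18/5.68 = 3.17, so power is about Φ(3.17 − 1.96) = 88.7%. For complete cases SE = √(2 × 900/47.7) = 6.14, and 20/6.14 = 3.26, so power is about 90%. Simulation gave 88.6% and 90.0%. Holding the SD unchanged after imputation, with the effect sized for exactly 90%, gives 86.6%.

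**Loss related to outcome.** Suppose 10% are lost in each arm, the VFS participants lost would have worsened by 10 points, and the CFS participants lost would have matched their arm mean of 10. VFS completers improve by 20. Truth: 0.9 × 20 + 0.1 × (−10) − 10 = 7. Carry-forward: 18 − 9 = 9, an error of 2 points in favour of VFS.

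An extreme case has no true effect, both arms improving by 10, SD 30, and exactly the worst responders lost at 15% (VFS) and 5% (CFS):

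| Analysis | Bias toward VFS | False positives favouring VFS (nominal 2.5%) |
|---|---|---|
| Carry-forward | 2.6 to 2.9 | 10% to 11% |
| Complete cases | 4.6 to 5.0 | 16.5% to 20% |

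The ranges are from repeated simulations. With the rates reversed, the biases are of similar size against VFS.

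**After V3.** For SWS and UPDRS-III a control participant who misses only V5 has a V4 value taken under VFS. A CFS value is carried forward only if V4 is missed as well. For FOG-Q, GAFQ and PDQ-39 there is no V4 value, so missing V5 alone is enough.

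**The case against.** The strongest reply is that at the only attrition figure the plan gives, with loss random and equal, the effect is small and conservative: 18 instead of 20, about 1.4 percentage points of power, and a false-positive rate that stays nominal. That stands, and it limits the severity. It does not rescue the rule, which gives no protection if loss differs by arm.

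Several stronger readings are tempting, but the document does not support them.

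- A reader might infer from the worst-responder case that carry-forward inflates false positives to about 10% and that a missing-at-random method would cure this. The 3:1 loss ratio and strict deletion of the worst responders appear nowhere in the article. In that case complete cases do worse, and without predictive covariates a missing-at-random method would match them. The figure is no argument for the replacement.
- A reader might infer that dropout will be related to outcome. The withdrawal reasons (safety, compliance, consent, serious disease) make this possible. None is defined by SWS response, and nothing shows that it would differ between blinded arms.
- A reader might infer that a participant who can no longer walk the course is credited with an earlier, better time. The article does not say that an uncompleted walk is coded as missing.
- A reader might infer that CFS values routinely stand in for VFS outcomes on the primary measure. The SWS test at V4 prevents this unless V4 is also missed.

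Sensitivity analyses may sit in an analysis plan that is not shown, so their absence from the article is not counted against it. The carry-forward rule itself is a stated choice.

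**Conclusion.** The point holds as a flaw that should be fixed, not as evidence that the trial will give a false positive. The mechanism follows from the stated rule and Table 1 alone: a participant lost before V3 contributes a baseline-phase SWS value to the 3-month comparison.

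The sizes rest on assumptions. With random, equal 10% loss the difference shrinks by 10%. With random 15%/5% loss and a 10-point improvement in both arms, a spurious difference of about 1 point appears, against whichever arm loses more. With outcome-dependent loss the direction and size are unknown, because the article gives no SD, no arm means and no attrition by arm.

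The carry-over of CFS values into the all-VFS period is a direct consequence of the schedule for FOG-Q, GAFQ and PDQ-39. For SWS and UPDRS-III it is conditional on V4 being missed too.

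**What to change.** 1. In the primary analysis, replace carry-forward with multiple imputation by randomised arm, using baseline SWS and UPDRS-III, or with a likelihood-based model valid under missing-at-random. State whether V1 or V2 is the SWS baseline.
2. Pair it with a delta-adjusted (tipping-point) sensitivity analysis that varies the assumed outcome of those lost separately by arm. This is essential, because the method in step 1 does not remove bias from outcome-dependent loss and can be more biased than carry-forward in the worst-responder case.
3. State that no value obtained under CFS is carried into the period when all participants receive VFS.
4. Carry-forward may remain as a sensitivity analysis.

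The cost is about one paragraph of plan wording and modest programming, with no new data. The article reports that enrolment is still under way, so the change can be made before database lock and unblinding.
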